## Abstract

**Background:**

Chronic heart failure requires a complex treatment regimen on a life-long basis. Therefore, self-care/self-management is an essential part of successful treatment and comprehensive patient education is warranted. However, specific information on program features and educational strategies enhancing treatment success is lacking. This trial aims to evaluate a patient-oriented and theory-based self-management educational group program as compared to usual care education during inpatient cardiac rehabilitation in Germany.

**Methods/Design:**

The study is a multicenter cluster randomized controlled trial in four cardiac rehabilitation clinics. Clusters are patient education groups that comprise HF patients recruited within 2 weeks after commencement of inpatient cardiac rehabilitation. Cluster randomization was chosen for pragmatic reasons, i.e. to ensure a sufficient number of eligible patients to build large-enough educational groups and to prevent contamination by interaction of patients from different treatment allocations during rehabilitation. Rehabilitants with chronic systolic heart failure (n = 540) will be consecutively recruited for the study at the beginning of inpatient rehabilitation. Data will be assessed at admission, at discharge and after 6 and 12 months using patient questionnaires. In the intervention condition, patients receive the new patient-oriented self-management educational program, whereas in the control condition, patients receive a short lecture-based educational program (usual care). The primary outcome is patients’ self-reported self-management competence. Secondary outcomes include behavioral determinants and self-management health behavior (symptom monitoring, physical activity, medication adherence), health-related quality of life, and treatment satisfaction. Treatment effects will be evaluated separately for each follow-up time point using multilevel regression analysis, and adjusting for baseline values.

**Discussion:**

This study evaluates the effectiveness of a comprehensive self-management educational program by a cluster randomized trial within inpatient cardiac rehabilitation in Germany. Furthermore, subgroup-related treatment effects will be explored. Study results will contribute to a better understanding of both the effectiveness and mechanisms of a self-management group program as part of cardiac rehabilitation.

**Trial registration:**

German Clinical Trials Register: DRKS00004841; WHO International Clinical Trials: = DRKS00004841

## Background

Chronic heart failure (HF) is a common, costly, disabling, and fatal medical condition encountered by a wide range of health care professionals in both primary and secondary care [1]. It is an illness that requires a complex treatment regimen over a life-long period. Therefore, self-care management/self-management is an essential part of successful treatment of patients with HF [2-6]. Meta-analyses/reviews provide evidence for the effectiveness of self-management interventions and patient education for HF-patients regarding knowledge, self-efficacy, self-management behavior, health-related quality of life, hospitalization and mortality e.g. [7-12]. However, studies show methodological shortcomings and further research is needed to determine independent effects of self-management interventions as well as different combinations of interventions [9].

Barlow and colleagues [13] described self-management as „the individual’s ability to manage symptoms, treatment, physical and psychosocial consequences and lifestyle changes inherent in living with a chronic condition, to effect the cognitive, behavioral and emotional responses necessary to maintain a satisfactory quality of life, so a dynamic and continuous process of self-regulation is established“. For HF patients, essential educational topics that should be covered include definition and aetiology, symptoms and signs, pharmacological treatment, risk factor modification, diet and exercise recommendations, sexual activity, immunization, sleep and breathing disorders, adherence, psychosocial aspects and prognosis, each associated with certain skills or self-management behaviors [3,5]. Thus, the focus on knowledge and providing information alone may not be sufficient, and guidelines recommend comprehensive HF education and counseling targeting skills and behavior [3-5]. Important research questions are evaluation of tailored programs, which includes specific educational strategies, identifying risk groups for poor self-care and effectiveness of innovative communication methods [4].

Generally, management of HF should be multi-professional and comprises several health care settings [14]. German guidelines recommend cardiac rehabilitation (CR) in particular for patients with HF caused by coronary heart disease or hypertension associated with specific educational needs and life-style changes [2]. CR in Germany [15] is predominantly offered as comprehensive inpatient treatment with a regular duration of three weeks. It is accessible for patients with myocardial infarction, surgery or catheter-based interventions after discharge from acute hospital care or patients with a chronic course of the disease and subsequent functional impairment. Although patient education is an essential part of CR [16] for HF, at the time of the conception of the study few standardized [17,18] and no evaluated educational group programs have been available for routine use so far. Moreover, many German patient education programs still lack certain quality requirements, such as the use of manuals, patient-oriented didactics, small-group format and evaluation of effectiveness [19,20]. Furthermore, theory-based techniques to foster health behaviors [21,22] are only rarely employed. In addition, few studies have compared different educational approaches applied within a multidisciplinary rehabilitation program in an inpatient setting e.g. [23-27]. Overall, further studies are needed to explore the effects of patient education programs, specific educational techniques and subgroups of patients who benefit most.

### Objectives

The aim of our study is to evaluate the short-, intermediate and long-term effects of a patient-oriented self-management educational group program as compared with a usual care program for HF patients receiving inpatient medical rehabilitation.

We hypothesize that the self-management education program is superior to usual care regarding self-reported self-management competence (primary outcome). In addition, we expect superior effectiveness of the new program regarding several self-management behaviors, such as symptom monitoring, physical activity, and medication adherence, as well as health-related quality of life and treatment satisfaction (secondary outcomes).

Moreover, moderator effects of (1) gender, (2) age, (3) education, and (4) type of rehabilitation - cardiac rehabilitation within 14 days after an acute cardiac index event (aCR) versus cardiac rehabilitation during the chronic course of disease without recent acute index event (cCR) - will be explored.

## Methods/Design

### Study design and data collection

The study is a multicenter cluster randomized controlled trial in four cardiac rehabilitation clinics. Clusters are patient education groups that comprise HF patients recruited within 2 weeks after commencement of inpatient CR. Participants will be recruited consecutively. In the intervention group (IG), patients will receive the new patient-oriented self-management educational program, whereas in the control group (CG), patients will receive a short lecture program (usual care).

Data will be assessed at admission (t1) and three follow-ups, i.e. discharge (t2) and after 6 (t3) and 12 months (t4) using standardized patient questionnaires. Figure 1 shows the study protocol diagram.

**Figure 1 F1:**
[figure not shown]
Study protocol diagram of data collection processes.

Cluster randomization was chosen for pragmatic reasons, i.e. to ensure a sufficient number of eligible patients to build large-enough educational groups, to protect the blindness of the sample and prevent contamination by interaction of patients from different treatment allocation during rehabilitation.

### Ethical aspects

The study conformed to the principles outlined in the Declaration of Helsinki (http://www.wma.net/en/30publications/10policies/b3/17c.pdf) and was approved by the Ethics Committee of the Faculty of Medicine, University of Würzburg on 19 April 2011 (reference number: 60/11). Participation in the study is voluntary and based on written informed consent. Eligible patients will be informed about all relevant aspects of the study at the beginning of rehabilitation. Furthermore, they are informed of the right to refuse to participate or to withdraw consent to participate at any time without reprisal.

### Participants

Eligibility criteria for participants are a diagnosis of chronic systolic heart failure (ICD-10: I50), left ventricular ejection fraction (LVEF) of 40 or less, and New York Heart Association functional classification (NYHA) of class II or III. Exclusion criteria are acute events of decompensation, cognitive impairment, inadequate German language ability, and severe visual or hearing impairment.

All participants admitted to the rehabilitation clinic during defined time periods (algorithm defined for each clinic) will be eligible for building a cluster (education group), with a minimum of 3 participants per group as a prerequisite.

### Intervention

German inpatient multidisciplinary CR [15] includes medical treatment, exercise therapy/physical training, health education, psychological support, relaxation, and social counseling and comprises 3 weeks on average. In this trial, a self-management group program is compared to a basic medical lecture (usual care).

Intervention group (IG). Patients in the intervention condition will receive a self-management educational program “Curriculum Heart Failure” (for details see Additional file 1) that consists of 5 patient-oriented, interactive sessions of either 60 or 75 minutes each, which are provided in small groups of a closed format (15 participants or less). The program is manual-based and interdisciplinary with sessions led by a physician, a nurse, a psychologist and a physiotherapist, respectively. In each session, patients are actively involved in the educational process using a combination of didactic methods (short lectures, group discussions, practice, partner work and individual work). Didactic materials include presentations, flipcharts, and two patient booklets (educational booklet with HF information and worksheets, symptom-monitoring diary for twelve months). Contents of the lessons include HF illness and treatment knowledge (e.g. aetiology, symptoms and signs, diagnostics, treatment options such as non-surgical device treatment, surgery, and medication) with regard to individual information needs of the participants. Furthermore, the program focuses on self-management behaviors (e.g. dietary restrictions, attention to deterioration signs/symptoms, daily weight and blood pressure monitoring) and medication adherence. To promote physical activity, theory-based intervention techniques [21] are applied (e.g. action and coping planning, self-monitoring). Additionally, illness related problems in everyday life and signs of emotional distress with regard to HF and coping strategies are discussed.

The patient education program was developed by an interdisciplinary group of health professionals (members of the patient education workgroup of the German Society for Prevention and Rehabilitation of Cardiovascular Diseases, DGPR) and scientists with regard to previous work e.g. [17,18,27]. Both topics and didactics incorporate research evidence, guidelines, and quality criteria for patient-oriented educational programs. Patient acceptance and manual-based feasibility were verified in a pretest of 8 groups (2 in each participating clinic). Patients and trainers evaluated the education program with short standardized questionnaires directly after each session. Additionally, some sessions were observed and rated. Overall, results showed high acceptance and good feasibility. Based on open responses, small modifications were made to optimize the manual, intervention techniques and materials.

Control group (CG). Control condition is one lecture of basic medical education given by a physician with duration of about 60 minutes. Information is mostly presented in a vertical manner. Contents include basic HF illness information on aetiology, symptoms and signs, pharmacological treatment, non-surgical device treatment, surgery, and self-management recommendations (e.g. symptom monitoring and health behavior). Patients will receive three handouts which comprise main information on HF, and worksheets to list own medications as well as to monitor weight and blood pressure.

### Outcomes and measurements

We evaluate the effect of the patient education program on patient-reported self-management outcomes as well as health-related quality of life and treatment satisfaction. Therefore, all outcomes pertain to the individual level. The primary outcome is patients’ subjective self-management competence. Secondary outcomes include behavioral determinants and self-management health behavior (symptom monitoring, physical activity, medication adherence), health-related quality of life, and treatment satisfaction. Outcomes are assessed by standardized, validated measures. To assess symptom monitoring/control, a new measure will be developed based on existing instruments [28] and program-content. For details on outcomes, questionnaires and measurement points, see Table 1.

**Table 1 T1:** Outcomes, measures, assessment

		**Assessment**			
**Outcomes**	**Measures**	**t1**	**t2**	**t3**	**t4**
Self-management competence (primary outcome)	Health education impact questionnaire heiQ, German version [29]. Subscales Self-monitoring and insight, Skill and technique acquisition	X	X	X	X
	Kansas City Cardiomyopathy Questionnaire KCCQ, German version [30]. Subscale self-efficacy	X	X	X	X
Determinants of behavior:					
Intention, action and coping planning, action control	HAPA-scales [31,32]	X	X	X	X
Medication beliefs	Beliefs about Medicine Questionnaire BMQ-D [33], German version	X	X	X	X
Self-management behavior:					
Symptom control	Questionnaire will be developed by our research group	X	---	X	X
Physical activity	Godin Leisure-Time Exercise Questionnaire [34], German modified version	X	---	X	X
Medication adherence	Medication Adherence Report Scale MARS-D, German version [35]	X	---	X	X
Health-related quality of life (disease specific)	Kansas City Cardiomyopathy Questionnaire KCCQ, German version [30]	X	X	X	X
Treatment satisfaction	Short questionnaire developed by our research group [36]	---	X	---	---

t1 indicates admission to rehabilitation; t2, discharge from rehabilitation; t3, 6 months after rehabilitation; t4, 12 months after rehabilitation.

Additionally, sociodemographic parameters (e.g. gender, age, marital status, education, occupation), as well as depression and anxiety (Patient Health Questionnaire, 4 item version PHQ-4 [37]), social support (ENRICHD Social Support Inventory ESSI [38]), smoking, and hospitalization after rehabilitation will be assessed. Medical data (e.g. diagnosis, NYHA, LVEF) will be provided by the attending physician.

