### Statistical methods

All statistical analyses will be performed using SPSS for Windows. Prior to analysis, missing patterns will be explored. Missing data in accordance with missing at random (MAR) assumptions will be imputed using a multiple imputation procedure. Missing values due to drop-out will be analyzed by pair-wise deletion. Non-response-analyses and drop-out-analyses will be carried out by independent group comparisons using *t* tests for continuous variables.

The analysis of the primary and secondary endpoints will be done according to the intention-to-treat principle. Treatment effects (between-group effects) will be evaluated separately for each follow-up time point using multilevel regression analysis [39,40], with treatment group as fixed effects (IG, CG), individuals nested in clusters (education groups) as random effects, and adjusting for baseline values [41]. Statistical significance (p < 0.05, 2-sided) and effect sizes [42] will be reported for all between-group differences. Furthermore, ICCs for primary and secondary outcomes will be reported.

Moderator analysis will be performed by including the moderator variable as an additional fixed factor or covariate and examining interaction effects. Significance levels for interaction effects will not be adjusted due to their exploratory nature.

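### The treatment-effect model for the three self-management behaviours uses one baseline slope for acute and chronic patients and no term for type of rehabilitation, which may give up a little precision

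*Protocol article*

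**What the plan says.** All places are in the protocol article.

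- **Timing (Table 1).** The footnote reads "t1 indicates admission to rehabilitation; t2, discharge from rehabilitation". Physical activity ("Godin Leisure-Time Exercise Questionnaire [34], German modified version"), medication adherence (MARS-D) and symptom control ("Questionnaire will be developed by our research group") are assessed at t1, t3 and t4, not at t2. No recall period is stated for any of them.
- **Rank (Outcomes and measurements).** The behaviours are secondary: "Secondary outcomes include behavioral determinants and self-management health behavior (symptom monitoring, physical activity, medication adherence), health-related quality of life, and treatment satisfaction".
- **Patient mix (Objectives, Background).** Type of rehabilitation is the fourth moderator: "cardiac rehabilitation within 14 days after an acute cardiac index event (aCR) versus cardiac rehabilitation during the chronic course of disease". The Background describes access to rehabilitation for patients with "surgery or catheter-based interventions after discharge from acute hospital care or patients with a chronic course of the disease".
- **Model (Statistical methods).** Each follow-up is analysed separately by multilevel regression with treatment group as fixed effect, "individuals nested in clusters (education groups) as random effects, and adjusting for baseline values [41". Moderators enter as an extra fixed factor or covariate with an interaction, in a separate exploratory analysis.
- **Power (Sample size).** 416 patients give power 0.80 for d = 0.3, and the article warns that power for smaller effects on secondary outcomes may be too low.

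**The concern.** Baseline adjustment sharpens a treatment comparison to the extent that the baseline predicts the outcome. Someone admitted days after an acute event and a hospital stay may answer questions on exercise, medicines and symptom monitoring from a different situation than someone admitted from the chronic course of the disease. If so, the slope of 6- or 12-month behaviour on the t1 score differs by type. A single slope is then a compromise that fits neither type well. Any difference in level between the types that the baseline does not explain also stays in the residual.

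What is at stake is precision on three secondary outcomes. The type variable must be recorded for the moderator analysis, so leaving it out of the treatment-effect model saves nothing.

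**Working it through.** **The plan's own figures.** For d = 0.3, two-sided 0.05 and power 0.80, a t-test needs 176 per arm, or 352 in total. The design effect is 1 + (10 − 1) × 0.02 = 1.18, and 352 × 1.18 = 415.4, so 208 per arm and 416 in total. Power at 208 per arm is 0.804 by the normal approximation. These match the article. No factor (1 − r²) appears anywhere, so the plan takes no credit for baseline adjustment. With a baseline correlation r of 0.3 or 0.5, power would be 0.840 or 0.902. A weak baseline loses part of that extra and cannot push power below 0.80.

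**Inputs for the check (assumptions, not in the documents).** Baseline-outcome correlation 0.5 in cCR and 0.1 in aCR; unit variances; equal means; aCR share p of 30, 50 or 70%.

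**Formulas.**
- Common slope: b = 0.5(1 − p) + 0.1p; residual variance = 1 − b².
- Separate slopes: residual variance = 1 − [0.25(1 − p) + 0.01p].
- The difference between the two is p(1 − p)(0.5 − 0.1)².

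| aCR share | b | Common slope | Separate slopes | Reduction |
|---|---|---|---|---|
| 30% | 0.38 | 0.856 | 0.822 | 3.9% |
| 50% | 0.30 | 0.910 | 0.870 | 4.4% |
| 70% | 0.22 | 0.952 | 0.918 | 3.5% |

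**Effect on the treatment contrast.** Suppose a between-cluster variance of 0.02 is part of these residual variances and is not reduced by the new terms. The variance of the contrast is then proportional to the residual variance plus 9 × 0.02 = 0.18. At 50% aCR it falls from 1.09 to 1.05, or 3.7% (3.2% and 3.0% at 30% and 70%). With 208 per arm, the standard error is √(2 × 1.09/208) = 0.102 against √(2 × 1.05/208) = 0.100. Power for d = 0.3 is 0.834 against 0.847.

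**Unequal means.** Let the aCR mean differ from the cCR mean by s at baseline and δ at follow-up, in within-type SDs, and put q = p(1 − p). The common-slope residual variance rises by q(δ − bs)²/(1 + qs²). The model with type and separate slopes is unaffected. At p = 0.5, δ = 0.3 and s = 0, the rise is 0.25 × 0.09 = 0.0225, and the reduction becomes 1 − 0.870/0.9325 = 6.7%. With s = −1 and δ = 0 the rise is 0.25 × 0.09/1.25 = 0.018, and the reduction is 6.3%. The extra gain vanishes only if δ = bs.

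**Bias of the treatment contrast.** Trials were simulated with 42 clusters of 10, ICC 0.02, correlation 0.6 in cCR and 0 in aCR, and an aCR baseline shift of 0 or −1 SD (2,500 runs per setting). With 50 or 80% aCR and a common slope, the mean estimate was 0.301 to 0.304 for a true 0.30, and rejection under the null was 0.045 to 0.053. Power was about 0.82 at 50% aCR and 0.79 at 80%. Adding type and its interaction with baseline raised it to 0.85–0.86 and 0.81.

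**Bias of the moderator interaction.** With correlations 0.5 and 0.1, 50% aCR, a −1 SD shift, a common slope and no true interaction, the mean interaction estimate over 4,000 runs was −0.003 (Monte Carlo SE 0.003), with 4.9% rejections. A fresh set of 4,000 runs, tested by ordinary least squares, gave −0.001 (0.003) and 4.9%.

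**The case against.** The strongest reply is that nothing in the plan is wrong. The type covariate is optional, covariate detail often sits in an analysis plan not shown here, only secondary outcomes are concerned, and the gain rests on assumed correlations. Most of that stands, and it sets the weight of the point: an improvement, not an error. It does not remove the point. The article does name the terms of its model, uses type of rehabilitation only elsewhere, and itself worries about power for secondary outcomes.

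A reader might also infer more than the documents support:

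- **That the t1 score does not show usual behaviour.** This depends on the recall period, which the article does not state and may leave to the questionnaires. Nor does it describe who gave medicines or monitored symptoms before admission.
- **That the treatment effect is biased.** t1 is at admission, and allocation is disclosed only after the group is built, about two days before the intervention (Randomization and allocation concealment). Any weakness of the score falls on both arms alike.
- **That the aCR/cCR moderator result is distorted by recovery.** The moderator enters as a fixed factor, so recovery shared by both arms goes into its main effect. The simulation shows no distortion.
- **That the trial is short of patients.** Set against a residual variance of 0.75 (r = 0.5 for everyone), the common slope looks 14, 21 or 27% less efficient at 30, 50 or 70% aCR. The plan never relies on that benchmark, and separate slopes recover only part of the gap.
- **That the t1 items should be reworded.** This would depart from validated instruments and make t1 differ from t3 and t4, and nothing in the documents shows that it would predict better.

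**Conclusion.** The point holds as a modest efficiency gain available at almost no cost. With a common slope and no type term, the treatment-effect models for physical activity, medication adherence and symptom control may leave residual variance about 4% higher than necessary (3.5 to 4.4% over 30 to 70% aCR). At 50% aCR that is roughly one percentage point of power for d = 0.3.

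The size rests on assumed correlations of 0.5 and 0.1 and equal means. It grows if levels differ by type in a way the baseline does not predict. If the two slopes and adjusted levels are in fact alike, the gain is nil. The treatment contrast, the moderator interaction and the planned primary power are not called into question.

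**What to change.** In Statistical methods, pre-specify type of rehabilitation (aCR/cCR) as a fixed covariate in the treatment-effect models. For physical activity, medication adherence and symptom control, add a type-by-baseline term. Leave out a treatment-by-type term here, so that the treatment coefficient remains one overall effect; that interaction stays in the exploratory moderator analysis.

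The cost is one or two model terms, which is negligible with about 416 analysed patients. No new data, questionnaire change or larger sample is needed. The terms should be fixed before outcome data are seen, so that the choice of covariates cannot depend on results.
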